# Heart Rehabilitation for All (HeRTA)

## A feasibility study

## Introduction

HeRTA is a partnership project conducted in close collaboration between Hvidovre Hospital, Rehabilitation Center Albertslund (municipality), local sports organizations, the Danish Heart Association, and Center for Clinical Research and Prevention (CCRP). A patient advisory board is involved throughout the project to ensure patient involvement including that decisions continuously focus on patient needs.

**The overall aim of HeRTA** is to develop and test the feasibility of a new, sustainable model for rehabilitation supporting vulnerable patients to take part in rehabilitation and promoting life-long activity for all patients with heart disease.

More specifically our goal is to:

- test if combined activities across sectors can increase the proportion of cardiac patients’ participating in rehabilitation
- test if the model improves the maintenance of lifestyle changes and enhances physical and mental functioning, quality of life, and self-care capacity among cardiac patients

The project is organized in three phases:

1. **An ongoing development phase**, where all partners including the patient advisory board participate in a partnership and co-creation process to develop model content and collaboration procedures
2. **A feasibility phase** with a small scale RCT-component, where we examine whether the intervention activities are feasible, acceptable, and may have positive effects for patients with heart disease
3. **A long-term follow-up and implementation phase**, in which sustainability of the intervention on patient activity is assessed and promising components are further tested.

## 2. Background

Half a million Danes suffer from heart diseases^1^, and heart disease often coincides with other chronic conditions, with the combination of heart disease and diabetes being the most prominent^2^. According to national guidelines, people with heart diseases should be offered rehabilitation to minimize consequences and prevent new cardiac episodes. Solid evidence exists on the benefits of multifaceted cardiac rehabilitation on patients' cardiovascular function, functional level, and survival^3^.

Today, half of the cardiac patients do not participate in rehabilitation, and vulnerable patients are more likely to decline participation^4^. Structural barriers during the transition between hospital and municipality make it difficult for patients to navigate in rehabilitation activities. Additionally, the probability of being offered rehabilitation is lower if patients live alone, are unemployed, have a short education, a low income or suffer from several chronic conditions^4^. Other barriers to participation are a poor financial situation, weak social relationships, logistic challenges, language difficulties, and cultural considerations^4–7^. Even after having participated in rehabilitation programs, many patients struggle to maintain new lifestyle habits^8^.

Currently, the content of cardiac rehabilitation is disease management, medical treatment, tobacco cessation support, physical exercise, psychosocial support, and guidance about alcohol and nutrition. Despite health professionals’ intentions to address the vulnerability, vulnerable patients are overrepresented among those who do not receive a referral to rehabilitation, who do not participate in rehabilitation, and who do not complete rehabilitation activities.

## 3. Feasibility phase

During the development phase, partners and a patient advisory board has developed a model of combined activities aimed at creating a coherent rehabilitation course addressing needs among all patients with a special focus on patients with vulnerability. The model has used identified barriers for rehabilitation participation and benefits as a starting point.

The rehabilitation process is initiated 14 days after discharge with rehabilitation needs assessment. At this point, all patients will receive an *information book* that provides relevant and thorough information and contact information to patients. The information book also contains information on the availability of *patient supporters* from the Heart Association that provide a 1:1 conversation to patients who wishes to talk to an experienced patient about their worries concerning life with cardiac disease. *Employer material* will help patients inform employers and gain their support for rehabilitation participation and a plan for returning to work. *Support café for relatives* will support relatives in dealing with their worries as well as in supporting cardiac patients.

Patients with vulnerabilities will have access to *patient education conducted in small groups* that utilize patient involving methods to target and provide information relevant to patients’ daily lives. In addition, patients with vulnerabilities may be referred to *pro-active counselling* where a cardiac nurse, psychologist, or social worker from the Heart Association calls the patient to provide targeted support to their specific worries and challenges. Finally, patients with vulnerabilities may receive *paid transportation* to ensure that finances are not an obstacle for commuting to Rehabilitation Center Albertslund.

During rehabilitation at hospital and municipality, collaboration with civil society provides a safe *transition to local sports associations* and the Heart Association’s *local area exercise groups*. *Follow up phone calls* from physiotherapists in the municipality support patients to continue physical activity.

### Design, materials, and methods

We use qualitative data on implementation and acceptability of intervention among partners and patients. An RCT component will assess potential effects on patient participation rates, health, and life quality. The process evaluation will be guided by Normalization Process Theory (NPT)^9^ and the Consolidated Framework for Implementation Research (CFIR)^10^. To ensure successful implementation and sustainability, partners will meet quarterly to evaluate experiences with patient pathways and collaboration across partners. At these meetings, necessary adjustments are agreed upon. In the initial three months, meetings are more frequent to allow for relevant adjustments. In the remaining 9 months, strong rationale for changes should be provided to protect the potential of the study’s RCT component. All changes in activities or procedures throughout the feasibility phase - including the rationale for adjustments - will be registered in field notes.

##### Patient recruitment

Patients, who meet the inclusion criteria:

1. Ischaemic heart disease, cardiac valve surgery, persistent atrial fibrillation, or heart failure
2. Resident in Hvidovre Hospitals uptake area
3. Cognitively functional
4. Physically able to participate in rehabilitation activities

will be invited to participate in HeRTA by health care professionals at the cardiac department, Hvidovre Hospital. If they accept, they will receive a link to REDCap^12^ where they are asked to consent to a) information exchange between partners and b) participation in the project. Vulnerability is assessed at baseline and defined as either a) a cut-off score of ≥ 5^11^ in the Tilburg Frailty Indicator questionnaire^12^ or b) need of language translator support during consultations.

**The control group** has access to usual care at the cardiac outpatient clinic: training (1 hour 2 times a week for 6 weeks), dietary training (2x3 hours), and cardiac education (2x3 hours). After or instead of hospital rehabilitation, the patient can be referred to municipal rehabilitation in Rehabilitation Center Albertslund: training (1 hour 2 times a week for 12 weeks), patient education (3x2 hours by a cardiac nurse and 1x2 hours by a dietician).

**Patients in the intervention group** will, in addition to usual care, have access to the abovementioned activities.

##### Registration of participation and sustainability

Partners register patients’ participation in all activities to monitor participation rates across sectors. Data from self-reported patient questionnaires are collected at baseline (background, and outcomes), 3, 6, 12, and 24 months (outcomes, and participation in rehabilitation activities). Physical activity in local community participation are also collected at 12 and 24 months after baseline.

### Questionnaires include:

- Tilburg Frailty Indicator^12^: physical, mental, and social vulnerability.
- Health Education Impact Questionnaire (HEIQ)^13^: positive and active engagement in life.
- SF-12^14^: Physical and mental health summaries (PCS and MCS).
- Nordic Physical Activity Questionnaire-short (NPAQ)^15^: physical activities in leisure time.

##### Qualitative data on patient experiences

The research team conducts qualitative semi-structured interviews with 20 patients to uncover their experience of the overall process, contact with health care professionals, the match between activities and rehabilitation needs, patient involvement, and intersectoral coordination. Patients will be selected based on criteria for maximum variation. Both patients with high and low levels of participation will be selected for interviews.

##### Qualitative data on implementation among professionals

Organizational characteristics and cultures as well as individual approaches among professionals will shape the implementation of activities. Field notes on adjustments in the intervention content, procedures, and changes in the context (e.g. organizational changes, changes in management/employees) will provide knowledge on the setting and the processes affecting the potential for the effect of the rehabilitation model. Observations and/or recordings of rehabilitation activities in hospital and municipality and Danish Heart Associations proactive counseling will provide insight into the actual content of the activities and the fidelity of the implementation. Focus groups with involved partners will uncover the professional’s experiences and reflections on screening and referral procedures, information exchange, intersectoral collaboration, and rehabilitation activities.

## 4. Evaluation

##### Descriptive analyses of the effect sizes

We will perform descriptive analyses of baseline characteristics. The primary outcome will be a) analyzed according to the intention-to-treat principle, b) sensitivity analyses of changes within/between the intervention and control groups will be carried out. If the power of data allows - explorative subgroup analyses will be carried out on those screened to be vulnerable. Estimated effect sizes will be calculated to inform future assessment of sample sizes in RCTs.

##### Qualitative evaluations

All data from workshops, interviews, and focus groups will be audio-recorded and transcribed verbatim. Interview transcriptions and field notes will be analyzed using systematic text condensation described by Malterud^16^. The analytical process will be inspired by principles from Collaborative Data Analysis^17^.

##### Patients’ experiences from the intervention

The analysis will assess whether patients experience their treatment and rehabilitation course as an integrated and coordinated effort helping them to live with their heart disease. The analysis will nuance the quantitative analysis and assess whether the model succeeds in tailoring rehabilitation activities to individual needs. The full rehabilitation package is not necessary or relevant for all patients with heart disease. Patients with vulnerabilities may need elaborate support and encouragement to deal with the mental and physical challenges of heart disease, while patients with resources may need less assistance. Rather they may need to be supported in continuing making healthy lifestyle choices and in using their local area and network to return to everyday life. In this analysis, gaps in the match between activities and patient needs will also be identified.

##### The implementation processes

The analyses of organizational experiences are inspired by the context, process, and outcome model ^18^. They will focus on the fit between the varying partnering institutions and the developed rehabilitation activities and collaboration procedures. The acceptability of the intervention among employees will be assessed continually to ensure their support for the implementation. Reach and fidelity of implementation will be assessed to provide relevant knowledge for interpreting and drawing conclusions on the potential of each intervention component.

##### Cost-effectiveness analyses

In order to compare the costs of the intervention towards the effects, a cost-effectiveness analyses will be carried out. This will be done by calculating a ratio where the denominator is the health gains measured by quality adjusted years of life (SF-12/SF-6D) and the numerator is the cost associated with the health gain obtained from the intervention, which will be the total cost of the intervention including resources used by the patients^19–21^.

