# Perspectives

Results from HeRTA will point to a model that is feasible and sustainable within the Danish healthcare system and forms a coherent rehabilitation pathway for people with cardiac disease. The model can be adjusted locally to fit the context in other rehabilitation locations and to ensure local stakeholder engagement. Our preliminary economic evaluation of financial cost and use of resources will operationalize the sustainability of the model. The results can be extrapolated to other chronic illnesses e.g. diabetes, COPD, and multimorbidity conditions. Chronic patients’ concerns and difficulties in terms of rehabilitation are mostly comparable across chronic illnesses.

HeRTA can form the basis for further targeted rehabilitation studies: a) rigorous RCT studies dissecting the effect of specific elements of the intervention that shows the greatest potential for positive benefits, and b) studies that test the generalizability across contexts to ensure transferability of results.

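### The cost-effectiveness numerator is a total cost with no control-arm cost subtracted, so the ratio is expected to be biased as a cost per QALY gained versus usual care

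*Protocol*

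**What the plan says.** Under Evaluation, the section on cost-effectiveness analyses defines both parts of the ratio. For the bottom, "the denominator is the health gains measured by quality adjusted years of life (SF-12/SF-6D". For the top, "the numerator is the cost associated with the health gain obtained from the intervention, which will be the total cost of the intervention", and resources that patients use are counted in it. The section mentions no control-arm cost and no cost difference between arms.

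The section on patient recruitment describes the comparator. The control group "has access to usual care at the cardiac outpatient clinic: training (1 hour 2 times a week for 6 weeks", plus dietary training and education. It adds that "After or instead of hospital rehabilitation, the patient can be referred to municipal rehabilitation in Rehabilitation Center Albertslund". Intervention patients "will, in addition to usual care, have access to the abovementioned activities". One stated goal in the Introduction is to "test if combined activities across sectors can increase the proportion of cardiac patients’ participating in rehabilitation".

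On the use of the economic work, the Perspectives section says: "Our preliminary economic evaluation of financial cost and use of resources will operationalize the sustainability of the model".

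**The concern.** A health gain obtained from an intervention is a contrast with what would have happened without it, which in this trial means the control arm. A cost per QALY gained needs the same contrast in its numerator. Here the cost is described first as that associated with the gain, which could be incremental, and is then specified as a total.

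The gap matters in this design for two reasons. The control arm uses services that cost money. The model is also meant to change how many patients use those services, so usual-care cost is expected to differ between arms if the model works.

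An analysis that followed the text literally would report a figure that is not incremental to usual care, and so could not be compared with cost-per-QALY figures that are.

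**Working it through.** The protocol states no cost, QALY or sample-size figure in the text at hand, so there is nothing to reproduce. The check compares the stated numerator with the incremental one. The denominator is taken to be the between-arm QALY difference in both ratios, so it cancels.

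**Usual care has a cost.** Scheduled hours in the section on patient recruitment:
- Hospital: 1×2×6 + 2×3 + 2×3 = 24 hours.
- Municipal: 1×2×12 + 3×2 + 1×2 = 32 hours.

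Municipal care may follow or replace hospital care, so a full course is 24, 32 or at most 56 hours. These hours are not converted to cost here. They show only that usual care is too large to ignore.

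**Inputs** (cost per patient, in units of the add-on cost):
- A = 1: cost of the added activities.
- U = 0.5, 1 or 2: cost of usual rehabilitation per participant (assumption).
- p0 = 0.5: control participation. The Background says that half of cardiac patients do not take part today; applying this to the control arm is an assumption.
- p1 = 0.5, 0.6 or 0.7: intervention participation (assumption).
- S = 0 or 0.5: saving in other care (assumption).

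**Formulas**
- Incremental cost = A + U(p1 − p0) − S
- Whole-arm reading of the stated numerator = A + U·p1
- Add-on reading of the stated numerator = A
- Error factor = stated numerator / incremental cost

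**Results** (selected rows, including the extremes of the full grid)

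| U | p1 | S | Incremental cost | Whole-arm factor | Add-on factor |
|---|---|---|---|---|---|
| 0.5 | 0.5 | 0 | 1.00 | 1.25 | 1.00 |
| 0.5 | 0.7 | 0 | 1.10 | 1.23 | 0.91 |
| 1 | 0.6 | 0 | 1.10 | 1.45 | 0.91 |
| 1 | 0.6 | 0.5 | 0.60 | 2.67 | 1.67 |
| 2 | 0.7 | 0 | 1.40 | 1.71 | 0.71 |
| 2 | 0.5 | 0.5 | 0.50 | 4.00 | 2.00 |

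Over the whole grid the factor is 1.23 to 4.00 on the whole-arm reading and 0.71 to 2.00 on the add-on reading.

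**Direction.** The whole-arm numerator exceeds the incremental cost by (A + U·p1) − (A + U(p1 − p0) − S) = U·p0 + S. That is the control arm's usual-care cost plus any saving, so the ratio is too high. The add-on numerator differs from the incremental cost by S − U(p1 − p0). The ratio is too low when the extra usual care costs more than is saved, too high when it costs less, and right when the two are equal.

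**The case against.** The best defence is that the intervention is an add-on. If usual-care and other resource use were equal in both arms, the cost of the added activities would be the incremental cost, and the factor would be 1.00. The opening words of the numerator's definition can be read that way. The clause on resources used by patients might also be meant to cover the extra rehabilitation sessions that the model prompts.

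Part of this stands. A reader might infer that the reported cost per QALY is bound to be wrong, and the text does not show that. But equal use in both arms would mean that participation had not risen, or that any rise was exactly offset by savings. The first would be a failure of the project's own goal. The resource clause does not settle the matter either: sessions prompted by the model can be identified only by comparison with the control arm, which the definition leaves out.

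Three stronger inferences also go too far.
- Taking the added activities at 20% of usual-care cost, with every patient in both arms using full usual care, gives (1 + 0.2)/0.2 = 6-fold. No cost in the protocol supports that share. If usual-care cost is equal in both arms, the add-on reading is also exactly right.
- A reader might take the ratio to decide whether the model is sustainable. The Perspectives section ties sustainability to financial cost and resource use, without naming the QALY ratio, and no threshold or decision rule depends on it.
- The precision of the ratio in a small trial, and how to present its uncertainty, are matters commonly left to an analysis plan. They are not faults in this text.

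**Conclusion.** The concern holds as an expected bias. As written, the numerator is a total cost set against a QALY gain, while the comparator has its own cost and the model aims to shift it. Under the assumed costs, the stated ratio is 1.23 to 4.00 times the incremental one if the total covers the whole intervention arm, and 0.71 to 2.00 times if it covers the added activities only. The two agree only on the add-on reading with no net change in other resource use. The size depends entirely on assumed costs; the direction depends on which reading is used and on any savings.

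This should be fixed but is not critical. The economic evaluation is described as preliminary, it sits within a feasibility study, and the primary outcome is unaffected.

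**What to change.** In the section on cost-effectiveness analyses, define the numerator as mean cost per randomised patient in the intervention arm minus the same mean in the control arm. Count the same items in both arms: hospital and municipal sessions, Heart Association services, transport, and resources borne by patients. Define the denominator as the between-arm difference in SF-6D QALYs.

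The cost is a change of wording and a little more costing work for the control arm. Partners already register participation in all activities, according to the section on registration of participation and sustainability. Outcome questionnaires run at baseline and at 3, 6, 12 and 24 months, and SF-12 is among them. The drawback is that the result may look less favourable.

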## 6. Ethics approval

A data handling plan has been accepted by the Knowledge Center for Data Reviews, the Capital Region of Denmark (journal-nr.: P-2020-905). Approval is not needed from the National Committee of Health Research Ethics ^22^. The study is registered at ClinicalTrials.gov^23^, identifier: NCT05104658.

## 7. Deliverables from the HeRTA feasibility study

The following deliverables are tangible outcomes of the project:

- Collaboration model across hospital, municipality, patient organization and local sports associations
- Feasible patient-targeted rehabilitation activities across sectors
- Identification of promising components to increase participation in rehabilitation and physical activity in local sports associations
- Tools to engage patients with vulnerability in rehabilitation

### Communication plan

We provide an evidence-based contribution to the debate on cardiac rehabilitation and social inequalities in health and healthcare. The target groups for our communication are the research community; health professionals across sectors including leaders and key persons; civil society (e.g. patient organizations); and cardiac patients.

Findings will be presented in meetings, conferences, and written material, such as fact sheets and articles in peer-reviewed scientific journals and popular science journals and channels. We will communicate through the Heart Foundation (Magazine and conference(s)) targeting cardiac patients and health professionals.

# Perspectives

Results from HeRTA will point to a model that is feasible and sustainable within the Danish healthcare system and forms a coherent rehabilitation pathway for people with cardiac disease. The model can be adjusted locally to fit the context in other rehabilitation locations and to ensure local stakeholder engagement. Our preliminary economic evaluation of financial cost and use of resources will operationalize the sustainability of the model. The results can be extrapolated to other chronic illnesses e.g. diabetes, COPD, and multimorbidity conditions. Chronic patients’ concerns and difficulties in terms of rehabilitation are mostly comparable across chronic illnesses.

HeRTA can form the basis for further targeted rehabilitation studies: a) rigorous RCT studies dissecting the effect of specific elements of the intervention that shows the greatest potential for positive benefits, and b) studies that test the generalizability across contexts to ensure transferability of results.

